### *Study 2*

- 2) Interpreters trained in the MINDSET program will show an improvement in the quality of interpreted communication for dementia assessments at 3 months and 6 months following the intervention, when compared to their baseline scores.
- 3) Interpreters trained in the MINDSET program will show a greater improvement in the quality of interpreted communication for dementia assessments at 3 months and 6 months following the intervention, when compared to the control group's scores.

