## 5 Study 2 – Randomized control trial of training

Study 2 will be a randomized control trial (RCT), conducted to evaluate whether the training package developed during Study 1 fulfils our primary project aim of improving the quality of interpreter communication in a cognitive assessment for dementia. The trial will be a 6-month wait-list RCT with a parallel design, conducted with a target of 150 interpreters in equal allocation (75 in the intervention group and 75 in the control group).

Outcomes will be assessed at baseline ( $t_0$ ), post-intervention (3m after baseline;  $t_1$ ) and follow-up (6m after baseline;  $t_2$ ). The baseline covariates will include characteristics of interpreters (age; sex; ethnicity; location; educational and economic attainments; and NAATI credential status).

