### **5.5 Sample size justification**

The primary outcome is a score calculated using the method described above and based on that done by Ono et al [24]. A sample size of 120 (60 test and 60 control) participants (interpreters) is sufficient to detect with 80% power and alpha of 0.05, a difference in control and test group means of 1.3 with standard deviation of 2.5 (i.e. means of 2.91 control and 4.21 test in Ono et al[24]). The calculations are the customary ones based on normal distributions[33]. The target sample size is set at 150 interpreters (75 test and 75 control) to include oversampling for participant withdrawals, and because we see no foreseeable adverse effects for either group resulting from participation in the trial.

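### Hypothesis 3 requires benefit over control at both 3 and 6 months, but the stated 80% power covers one comparison at an unnamed visit

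*Protocol*

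**What the plan says.** Hypothesis 3 in Protocol Section 2.2 is the trial's only between-group hypothesis. It states that trained interpreters "will show a greater improvement in the quality of interpreted communication for dementia assessments at 3 months and 6 months following the intervention", relative to the control group. Section 5 schedules assessments at baseline, 3 months (post-intervention) and 6 months (follow-up).

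Section 5.5 says that 120 participants, 60 per arm, "is sufficient to detect with 80% power and alpha of 0.05, a difference in control and test group means of 1.3", with a standard deviation of 2.5, and that "The calculations are the customary ones based on normal distributions". No visit is attached to that difference. The target of 150 is set "to include oversampling for participant withdrawals", and Section 7.4.2 confirms that 60 per arm is the number needed to power the trial.

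Section 5.6 plans a mixed model with time as a three-level categorical factor. Neither it nor any other section names a primary visit, a testing order or a combined test over the two follow-up visits.

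**The concern.** The hypothesis makes two between-group claims and the sample size supports one. A trial sized at about 80% for a single comparison has a smaller chance of succeeding on two, unless the two results are almost perfectly correlated or the analysis is more precise than the sizing assumed. The stated 80% is therefore not the power of the hypothesis as written.

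The silence about visits also matters at reporting. A benefit at 3 months that is not seen at 6 months is a natural outcome for a training trial, and the reverse is possible. Read literally, Hypothesis 3 fails in both cases. With no visit named as primary, though, the visit that was significant could be presented as the main result once the data are seen.

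**Working it through.** **Inputs from the protocol (Section 5.5).** Difference 1.3, SD 2.5, so a standardised difference of 1.3/2.5 = 0.52; 60 per arm; alpha 0.05; power 80%; normal-theory comparison of two means. Sidedness is not stated.

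**Reproducing the stated size.** Per arm, n = 2(z_alpha + z_power)²(SD/difference)².
- Two-sided 0.05: 2 × (1.960 + 0.842)² × (2.5/1.3)² ≈ 58.1, rounded up to 59 per arm (118 in total), in line with 120.
- One-sided 0.05: 2 × (1.645 + 0.842)² × (2.5/1.3)² ≈ 45.7, so 46 per arm, which does not match.

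The calculation is therefore taken as one two-sided comparison. At 60 per arm the noncentrality is 0.52 × √(60/2) = 2.848, and power is Φ(2.848 − 1.960) = 81.3% (80.6% with the t distribution). The arithmetic of 120 is sound, and it leaves almost no margin for a second test.

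**Two visits, unadjusted.** Treat the 3-month and 6-month test statistics as bivariate normal, each with mean 2.848 (the same effect at both visits, an assumption) and correlation ρ. The protocol gives no ρ, so a range is shown.
- Power for both = P(Z1 > 1.960 and Z2 > 1.960).
- Error if either is accepted = P(|Z1| > 1.960 or |Z2| > 1.960) with both means zero.

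| Assumed ρ | Power for both, 60 per arm | Per arm for 80% on both | Type I error if either visit were accepted |
|---|---|---|---|
| 0.3 | 68.5% | 75 | 9.5% |
| 0.5 | 70.5% | 73 | 9.1% |
| 0.7 | 72.9% | 70 | 8.4% |
| 0.8 | 74.5% | 68 | 7.8% |

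At ρ = 0 power for both is 66.1%; at ρ = 0.9 it is 76.5%. When both visits are required, each at 0.05, the chance of a false claim cannot exceed 0.05, so the last column applies only under an either-visit rule.

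**Using the baseline score.** Assume all three scores share one correlation r (also not in the protocol). Baseline adjustment multiplies the variance by 1 − r² and makes the correlation between the two adjusted results r/(1 + r). Change scores multiply the variance by 2(1 − r) and have correlation 0.5.

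| Assumed r | Power for both, baseline-adjusted | Power for both, change scores |
|---|---|---|
| 0.3 | 73.3% | 52.3% |
| 0.5 | 83.6% | 70.5% |
| 0.7 | 96.0% | 92.4% |

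All figures are at 60 per arm. With baseline adjustment the shortfall is gone by r = 0.5; at r = 0.3 it remains.

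**The case against.** **Baseline information may close the gap.** The planned mixed model includes the baseline visit and the hypothesis concerns improvement, so an unadjusted calculation may understate the precision of the analysis. This stands, and it is why the size of the shortfall is uncertain. It does not rescue the stated figure: Section 5.5 is an unadjusted calculation, takes no credit for baseline and gives no correlation from which a reader could do so.

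**The recruitment target gives slack.** If all 75 per arm were retained, unadjusted power for both visits would be about 80% to 84% for ρ from 0.3 to 0.8. But the extra 30 (30/150 = 20%) are set aside for withdrawals, and Section 7.4.2 treats 60 per arm as the powered number.

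**The analysis plan may settle it.** Testing order across visits is often left there, and that plan is not shown. Its absence from the protocol is not the fault raised here. The fault is a mismatch between two statements that the protocol does make. A later document naming one primary visit would depart from Hypothesis 3 as worded, so the protocol text would still need correcting.

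**The visits are labelled differently and the model lists one group term.** The labels post-intervention and follow-up do not rank the visits. A single group term without a group-by-time interaction would average over baseline as well as follow-up, which is not what Hypothesis 3 claims.

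**Stronger readings that are not supported.** A reader might infer that the design delivers neither its power nor its error rate. No reading makes both fail. If both visits are required, alpha holds. If either suffices, power at 60 per arm is about 94% to 88% for ρ from 0.3 to 0.8 (2 × 81.3% minus the power for both), and only the error rate fails. Nor does the protocol contain an either-visit rule. A reader might also expect far lower power if the effect fades by 6 months; the protocol gives no 6-month effect, and such a loss would come mainly from the smaller effect and not from requiring two visits.

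**Conclusion.** The concern holds in a limited form. The stated 80% power belongs to one two-sided comparison at an unspecified visit, while the only between-group hypothesis requires success at two. On the protocol's own unadjusted inputs, power for both visits at 60 per arm is about 68% to 74%, some 6 to 12 points below the stated figure, with alpha intact. An inflated error rate, about 8% to 9.5%, would arise only if a win at either visit were accepted at 0.05 each, and the wording does not say that.

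The size rests on three assumptions: a two-sided test, inferred because it reproduces the stated size; equal effects at the two visits; and a between-visit correlation of 0.3 to 0.8. Baseline adjustment could remove the shortfall if the scores correlate at about 0.5 or more. Confidence is high that the two statements do not match and moderate on how much power is lost. The protocol should be corrected.

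**What to change.** Name one follow-up visit as the primary between-group comparison and say in Section 5.5 that the existing calculation refers to it. Test the other visit at 0.05 only if the first is significant, and reword Hypothesis 3 to match. The stated 80% and 0.05 then apply without any change to the sample size, and the choice of visit can no longer be made after the data are seen.

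If both visits must stay required, restate the power in Section 5.5 as joint power: about 70% to 75% unadjusted at 60 per arm for correlations of 0.5 to 0.8, and slightly lower (68.5%) at 0.3. Give the assumed correlation, and any credit taken for baseline adjustment, as explicit assumptions. Reaching 80% on both visits without adjustment would need 68 to 75 evaluable per arm for ρ from 0.8 to 0.3.

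The first option costs wording only. Its downside is that the second visit becomes confirmatory only after the first succeeds, and the 80% does not extend to it: the chance of reaching significance there within the sequence is the joint power shown above.

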### *Study 3*

- 4) The MINDSET program will be found to be feasible, acceptable, and effective by interpreters, their managers, and clinicians who frequently work with CALD clients in dementia related services.

## 2.3 *Theoretical framework*

We apply the RE-AIM [14] theoretical framework to co-design an intervention that creates the implementation outcomes necessary for achieving a sustainable and scalable intervention [15] (Table 1). This framework has been used in over 430 studies to develop public health initiatives and considers the following elements: reach, effectiveness, adoption, implementation, and maintenance [15].

Table 1. Application of the RE-AIM framework in MINDSET

| Theory         | Method                                                                | Activities                                                                                                                                                                              |
|----------------|-----------------------------------------------------------------------|-----------------------------------------------------------------------------------------------------------------------------------------------------------------------------------------|
| Reach          | Qualitative interviews, Co-design workshop, RCT, Implementation study | We will assess how co-design methods strengthened the reach and uptake of the training and assess the extent to which interpreters remain engaged via the RCT and implementation study. |
| Effectiveness  | RCT                                                                   | We will assess the extent to which the training intervention effected interpreter communication quality.                                                                                |
| Adoption       | Co-design, Implementation study                                       | We will work with interpreters and clinicians to identify during the co-design and implementation how the training will be applied in practice.                                         |
| Implementation | RCT, Implementation study                                             | We will identify factors that are likely to influence scale-up of the training and use the lessons learned to advise our partners for national scale-up.                                |
| Maintenance    | Knowledge transfer.                                                   | We will give the training package to NAATI and promote it among our industry partners to maintain the training.                                                                         |

### 3 Project governance and steering group

A project Steering Group has been formed, consisting of our industry partners, Chief Investigators (CIs), two CALD consumers, two interpreters, and the Project Manager. The Steering Group will meet twice a year. This group will provide oversight of the research, offer guidance about the appropriateness and applicability of the intervention, and ensure that the intervention aligns with concurrent and planned policy and regulatory initiatives. The Steering Group will also meet for the co-design workshops and for a Stakeholder Forum towards the end of the project. A project Executive Team will include the CIs, AIs, and Project Manager. The Executive Team will be responsible for implementation of the project and all related activities. The Project Executive Team will meet every second month. The Implementation Team, consisting of CI [name], the Project Manager, and the NAATI assessors (Study 2/Year 2) will meet monthly.

The project is a partnership between the research team, key representatives from the interpreting industry, Dementia Australia, and the Migrant and Refugee Health Partnership. It has funding from several sources, including our interpreting industry partners and through a grant from the NHMRC Partnership Projects 2020 (APP2005759). Industry funding partners will be involved in the project in the Steering Group in an advisory capacity and will support recruitment efforts and dissemination of the final product. However, funding partners will be not involved in the collection or analysis of data, nor in the reporting of project outcomes, except for data gathered by NAATI during the monitoring phase of the implementation study (see section 6.2).

## 4 Study 1 – Co-design of the training

Study 1 will use information gathered from multiple sources and apply a co-design approach to develop an evidence-based, co-developed and user-tested training package. Study 1 will therefore involve the following stages:

- 1.1) Review of literature and existing training
- 1.2) Co-design workshops with stakeholders
- 1.3) Development of training and education materials
- 1.4) User-testing of training

### 4.1 *Review of literature and existing training*

A comprehensive review of any literature on language interpreting for people with dementia, during dementia-related consultations, or of cognitive assessments will be conducted using a scoping study methodology [16]. We will also conduct an environmental scan to identify any existing training materials or interventions designed to increase interpreters' competencies and knowledge when working with clients with dementia or interpreting for cognitive assessments. This review will ensure the development of training materials is informed by the latest evidence, and it will support us with mapping out how training materials will be targeted toward achieving the project aims.

#### 4.1.1 Method

Once consent has been obtained, interviews will take place either in-person, over Microsoft Teams, or over telephone and will be audio-recorded. The interviews will be short and flexible - up to 30 minutes in duration – and will take into the needs of the person with dementia and the availability of any support they require. People with dementia may choose to complete the interview with a family carer or support person present. However, they will not be required to have a carer or support person present if they do not wish to have one. Interviews will consist of questions about the participants' experiences with interpreters, what interpreters did well to support their needs, what interpreters could improve upon, and any other things that interpreters should know when interpreting for people living with dementia.

We recognize there is a potential conflict of interest if interpreters are used for these interviews. For this reason, participants will be interviewed by bilingual NARI researchers, who have previous qualitative interviewing experience from the *Moving Pictures* project (Curtin University HRE2017-0758). Participants will be given the choice of whether they speak in English or their other primary language during interviews.

### 4.2 *Co-design workshops*

This stage recognises the importance of working with interpreters, clinicians, and family carers to better understand their mutual needs and expectations, and thereby develop training that allows interpreters to perform optimally in their role. Using a co-design technique ensures that the MINDSET program will genuinely meet the needs of older clients, and the result will be a program more relevant to all stakeholder due to the fact that they have been involved in the design and evaluation of it.

Co-design emphasises the importance of lived experience, collaboration, and participation of all stakeholders in the research [17]. Interpreters, clinicians, and carers will collaborate to identify and address the challenges and issues from multiple perspectives, and design solutions to enhance desirability, acceptability and usability of the training package [17].

*Workshops will be conducted online (via Teams)* to minimize the risk of the project being delayed by any COVID-19-related restrictions. Online workshops also overcome the need for participants to travel to a central location, which enables better access for some participants.

#### **4.2.1 The World Café methodology**

The workshops will be conducted online using the World Café methodology, which is a type of focus group that enables participants to be part of evolving rounds of dialogue with three or more people while simultaneously being a part of an interconnected conversation with the other groups at the workshop [18]. The World Café methodology regards all participants as experts of their own lived experience and life-worlds, and the focus is on encouraging the sharing of diverse perspectives rather than reaching consensus. The method is designed to facilitate a conversational greenhouse in which there is a rapid propagation of actionable knowledge and collective solutions [18].

The World Café methodology has been demonstrated to promote high quality consumer engagement and meaningful collaboration between stakeholders [19]. However, in order to mitigate the possibility that power imbalances between different participant groups (e.g. interpreters, clinicians, and people with dementia) means some views less heard than others, we will periodically use break out rooms to separate groups and allow space for them to reflect on their specific knowledge and experiences [20]. The research team will also encourage equal participation throughout the workshops, and actively manage group dynamics and conflict resolution.

We will utilize the Microsoft Teams inbuilt recording function to record workshops, provided that participants' voluntarily consent to being recorded. Research team members will also be present throughout the workshops, taking field notes of the conversations, and recording the outcomes of activities. Following the workshops, all records will be analysed by members of the research team for the purpose of designing the training modules. Workshop recordings may be transcribed, depending on project resources, and requirements. All notes, recordings and transcriptions will be subject to the project's data security and handling policy.

Participants will connect to the workshops via Microsoft Teams. We will assign participants to break out rooms, first placing participants of the same stakeholder group (e.g. interpreters, clinicians, and carers) together, then in rooms with a mix of stakeholders from a range of backgrounds and perspectives. CIs [name], [name], and [name] have successfully used these methods in their current research [21-23].

#### **4.2.2 Workshop participants and recruitment**

Alongside the research team and partners, up to 25 stakeholders will participate in the co-design workshops. Participant groups will comprise:

- 6-8 interpreters
- 5-7 clinicians (e.g. geriatricians, neuropsychologists, old age psychiatrists).
- 5 - 7 CALD family carers

Interpreters will be recruited for workshops through our interpreter industry partners, NAATI and AUSIT, who will use their internal mailing lists to issue calls for expressions of interest with contact details of the research team. To be eligible, interpreters must be NAATI credentialed with provisional certification or professional certification and 6+ months practicing experience. Interpreters will be remunerated by our industry partners according to a standard hourly interpreting rate for time spent participating in workshops.

CALD carers will be recruited for workshops by the NARI research team. NARI has contact with potential candidates who were previously recruited as participants in the *Moving Pictures* project, in accordance with that project's ethics protocol (Curtin University HRE2017-0758). NARI researchers will contact some of these candidates directly and issue a call for expressions of interest through the regular *Moving Pictures* newsletter. Any recruits will be required to review and complete a MINDSET written consent form. Each participating carer will be offered one \$100 gift card as an expression of gratitude for the time they spend in both workshops.

Clinicians will be recruited through the Australian Dementia Network – a professional network of clinicians and researchers. CI [name] is a member of the network. A call for expressions of interest, with contact details of the research team, will be issued through the network's internal mailing list. Clinicians will be offered \$500, \$250 per a workshop, for their participation. This is what we estimate it will cost to remunerate qualified medical professionals (e.g. general practitioners, specialists) for their time, including any backfill and other expenses they or their organizations incur from their participation in our workshops. If they are only able to attend one workshop, by arrangement with the research team, they can be compensated \$250.

### **4.2.3 Workshop schedule**

The co-design will comprise two half-day workshops, approximately 2 weeks apart. The workshop agendas will be scheduled as follows:

#### **4.2.3.1 Workshop 1**

Participants will be introduced to dementia. Then Participants will convene in break-out rooms and asked to identify the most challenging aspects of interpreter-mediated dementia assessment, and exemplars (existing or possible) of interpreter training initiatives that address these challenges. Participants will be allocated to break-out rooms according to their role (e.g. interpreters, clinicians, family carers).

Then participants will reconvene and they will be presented with the five interpreting domains critical to quality communication, as identified by international research [24, 25]:

- a) Phraseology: identifying frequently used phrases in cognitive assessment and medical encounters,
- b) Terminology: specific terminology,
- c) Code of ethics: knowledge and application of the relevant interpreter code of ethics,
- d) Contextual knowledge: medical interpreting in various situations (reception, cognitive assessment, medication administration guidance, and informed consent);
- e) cross-cultural communication.

Participants will be informed that the training will be designed around these five aims and they will be asked to comment and endorse them.

Then Participants will convene in break-out rooms in mixed groups to elaborate on preferred types of pedagogical learning to enhance uptake of the training.

